### 2.2. Recruitment

The study will be conducted in three public hospitals in eastern Spain (Hospital Lluis Alcanyis, Hospital General de Castellón, and Hospital Universitario de la Ribera), and in one hospital in the western part of the country (Hospital San Pedro de Alcántara de Cáceres). The four hospitals serve a total population of 500,000 inhabitants, with an average of 5000 births a year. The women will be included during the third trimester of pregnancy in the different primary care midwife consulting rooms of each of the participating centers.

The study exclusion criteria are: females under 16 years of age; women with cognitive impairments, language barriers, or illiteracy (not able to read Spanish); non-availability of a mobile device with internet connection; newborn infants with congenital malformations; twin or multiple pregnancies; and admission to the Neonatal Intensive Care Unit (NICU), prenatal death or stillbirth, or postpartum complications requiring admission of the mother to the intensive care unit (ICU). Women failing to respond to the automated messages from the platform after three attempts will also be excluded, in the same way as those women in the control group who have used the LactApp^®^ application on their own initiative. Figure 1 shows the monitoring to be carried out during the study.

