### 2.3. Randomization and Blinding

The women will be included during the third trimester of pregnancy in the different primary care midwife consulting rooms of each of the participating centers. After reading the information sheet and giving informed consent, the women will be registered on a webpage created for the purpose of the research and will be assigned to one of the groups (control or intervention) via a simple randomization process, until the estimated sample size has been reached. Randomization will be performed using Epidat v.4.2. [33], with groups of equal size.

Allocation concealment will be carried out, with blinding of the midwives in charge of recruiting the women, providing them with sealed, opaque and sequentially numbered envelopes to be delivered to each new participant wishing the participate in the study.

The research team will prepare the envelopes based on the random allocation sequence. Each envelope will contain a card with a QR code providing access to the study follow-up platform. Follow-up data collection will be conducted by another researcher blinded to the group status of participants. Only the data manager will have access to all of the integrated data (the data reported by the participating women through the surveys and the birth/postpartum data reported by the principal investigators).

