- Variables related to BF education received for 6 months: information/training in BF (none/previous information received from relatives, friends or health professionals (midwife, pediatric nurse, obstetrician, pediatrician)), consultation of texts, participation in birth preparation groups, nursing groups or postpartum groups, and the use of digital tools (yes/no/specify which).

- LactApp^®^ use will be assessed from women’s reports on the acceptability and convenience of the mobile application while during use. Data will be collected on the number of connections made, time of use, and topics consulted. All of these data will be provided by the company in an anonymized form. No private information resulting from the mobile application will be collected.

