### 2.8. Data Analysis

An analysis will be performed of the baseline characteristics between the group of possible losses to follow-up and the group of women that complete follow-up, based on two-input tables and the comparison of means, using the Fisher exact test or Mann–Whitney U-test, as applicable.

Testing of the homogeneity of groups will be completed regarding the baseline variables and birth-related parameters and the suspension of BF at 6 months, using two-input tables and the chi-square test (χ^2^) or Fisher exact test, as applicable, while the comparison of means will be performed using the Mann–Whitney U-test.

A per-protocol (PP) analysis and intention-to-treat (ITT) analysis will be carried out. In the PP analysis, continuous variables will be reported as the mean and standard deviation (SD), or as the median and interquartile range (IQR) in the case of a non-normal data distribution, while categorical variables will be reported as frequencies and percentages. Data normality will be assessed using the Kolmogorov–Smirnov test.

In the ITT analysis, sensitivity referring to losses during follow-up will be assessed, with the response variable of the intervention group being assigned the worst result possible (suspension of BF at 6 months) and the control group being assigned the best result possible (no suspension of BF). Evaluation of the differences in response variable between the two groups will be performed, with all randomized subjects, applying the chi-square test.

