## 3. Discussion

The purpose of this trial is to explore the impact of an intervention program based on the use of a mobile application in maintaining breastfeeding up to 6 months postpartum. The null hypothesis is that the LactApp^®^ mobile application does not improve the maintenance of BF at 6 months postpartum versus usual clinical practice.

Breastfeeding is not only a physiological process but also entails cultural learning, causing mothers to actively seek information [19]. Nowadays, online communication options have been incorporated into this active search for information [24], and the adoption of such new technologies has been associated with improved nursing rates [43,44]. Although not under professional influence, the use of information and communication technologies in daily life must be acknowledged, and such tools should be used as a means to disseminate quality information based on evidence [45]. In 2018, 67.3% of the Spanish population used the Internet to obtain information on health, and in this regard, mobile applications constitute a growing contribution in the field of information and communication technology [45]. Health professionals must make efforts to consolidate their position as a reference in these new settings as well. If they prove effective and acceptable to the population for which they are intended, instruments of this kind could be introduced as intervention tools for promoting and maintaining BF.

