## 4. Limitations

The present study has its limitations. The level of adherence or decisions of the pregnant women when the issue of breastfeeding is raised during the monitoring of pregnancy may depend on a number of factors such as the type of information given to the women and the way in which the health professionals communicate with them. In effect, we consider that favorable health outcomes to be largely dependent upon the complex interaction between the health professional and the patient or user. However, the aim of our study is to explore the patient-related factors that facilitate or complicate BF, such as poor health literacy, with reference to the body of literature cited in the protocol. Since there is currently no standardized and protocolized mechanism for determining the skills of pregnant women in making effective use of the information provided, we consider it prudent to assume that the information supplied will be more or less the same for each woman (LactApp^®^ + professional), and that women with limited HL will be more prone to making suboptimal decisions as a result. In view of these shortcomings, we feel that it will be difficult to find compensation mechanisms for these women. Logically, this does not obviate the individual efforts which the professionals may make to solve problems such as poor understanding or language issues. Nonetheless, we believe that the added complexity of trying to systematize and define such efforts falls beyond the scope of our study. Furthermore, a contamination effect could occur among the women participating in the study, relating to the exchange of information regarding the use of the mobile application. This could be detected through the periodic electronic nursing follow-up surveys, evaluating whether the women in the control group make use of online tools. Such use would be reason for exclusion from this study. Another limitation may be the number of losses over follow-up. The self-completed electronic survey via the Internet has many advantages such as speed of data collection, lower cost, and can provide an attractive design for the respondent [41]. The downside is that there may be a lower response rate, which may affect the results obtained. In order to control for such selection bias and break of randomization, an analysis will be performed of the characteristics of the group of dropouts, along with an intention-to-treat analysis.

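### Control women are excluded after randomization for using LactApp (or, in the Limitations, online tools), a one-arm rule that conflicts with the ITT analysis and leaves the PP comparison unprotected

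*Protocol article*

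**What the plan says.** - Section 2.3: women are randomized in the third trimester, when they "will be assigned to one of the groups (control or intervention) via a simple randomization process".
- Section 2.2: among the exclusions, non-responders to the platform "will also be excluded, in the same way as those women in the control group who have used the" LactApp application of their own accord. A woman belongs to the control group only once allocated, so this condition cannot be a pre-randomization eligibility criterion.
- Section 4, on contamination between participants: "This could be detected through the periodic electronic nursing follow-up surveys, evaluating whether the women in the control group make use of online tools". The next sentence reads: "Such use would be reason for exclusion from this study".
- Section 2.8: both a PP and an ITT analysis are planned and neither is called primary. The ITT comparison is made "with all randomized subjects". Losses to follow-up are set to suspension in the app arm and to no suspension in the control arm.
- Section 2.7: use of digital tools is recorded, with the tool specified. LactApp use is taken from women's own reports and from company data on connections, time and topics.

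The article states no exclusion for app-arm women who never open the app or who use other tools.

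**The concern.** The rule acts on behaviour after allocation and in one arm only, so the retained controls are no longer the randomized comparator of the app arm. Controls who look for LactApp themselves may differ from the others in their chance of stopping breastfeeding. Removing them then moves the control suspension rate even if the app does nothing.

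The two statements of the rule also differ. Section 2.2 names LactApp; section 4, read literally, covers online tools. Neither fits an analysis of all randomized women, and section 2.8 does not say whether an excluded control is dropped, counted as a loss, or kept with her observed outcome. These three options give different answers to the primary question.

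**Working it through.** **Plan's own figure.** The plan gives no figure for this rule, so there is none to reproduce.

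**Inputs from the article.** Control suspension of 60%, app-arm suspension of 40%, alpha 0.05, planned power 85%, 399 women in total and 20% loss (section 2.4). Evaluable per arm: 399 / 2 x 0.8 = 159.6, about 160.

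**Assumptions.** The article gives neither f, the share of controls excluded, nor pu, their suspension rate. I take f = 20% and vary pu on both sides of 60%. There is no true effect, so both arms suspend at 60%. Other losses are ignored to isolate this rule.

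**Reading 1: excluded controls are dropped** (PP, or any analysis without them).

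Remaining control rate = (0.60 - f x pu) / (1 - f), with 160 app women and 160 x 0.8 = 128 controls. The chance of a significant false benefit is Phi[(d - 1.96 x se0) / se1], where d is the control minus app rate, se0 the pooled and se1 the unpooled standard error.

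| pu | Remaining controls | Shift | Chance of a significant false benefit |
|---|---|---|---|
| 40% | (0.60 - 0.08) / 0.8 = 65.0% | 5.0 points towards the app | 13.7% |
| 45% | (0.60 - 0.09) / 0.8 = 63.75% | 3.75 points towards the app | 9.5% |
| 60% | (0.60 - 0.12) / 0.8 = 60.0% | none | 2.5% |
| 70% | (0.60 - 0.14) / 0.8 = 57.5% | 2.5 points against the app | 0.8% |

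First row in full: pooled rate = (160 x 0.60 + 128 x 0.65) / 288 = 0.622; se0 = 0.0575; se1 = 0.0572; (0.05 - 1.96 x 0.0575) / 0.0572 = -1.09, which gives about 0.137.

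**Reading 2: excluded controls are counted as losses** and set to no suspension under section 2.8.

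Control rate = 0.60 - f x pu.
- pu = 40%: 0.60 - 0.08 = 52%, 8 points against the app.
- pu = 45%: 0.60 - 0.09 = 51%, 9 points against the app.
- A higher pu makes the shift larger: at 60% it is 0.2 x 0.60 = 12 points against the app.

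**Reading 3: excluded controls are kept with observed outcomes.** The shift is zero, but the women are then not excluded from the study.

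**Cost of keeping them.** Suppose 20% of controls use the app and gain its full planned effect. The control rate becomes 0.8 x 0.60 + 0.2 x 0.40 = 56%, and the difference falls from 20 to 16 points. With 160 per arm and two-sided alpha 0.05:
- 60% v 40%: (0.20 - 1.96 x 0.0559) / 0.0548 = 1.65, power about 95%.
- 56% v 40%: (0.16 - 1.96 x 0.0559) / 0.0551 = 0.92, power about 82%.

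**The case against.** A reader might infer that the rule biases the trial towards the app. The documents do not support that as a general statement. The pro-app shift arises only where these women are dropped, and only if they would have suspended less often than other controls. The article gives no rate for them. Section 2.5.3 describes LactApp as an automated consultation, so some controls may turn to it because breastfeeding is going badly; the shift could then be nil or run the other way. Under the loss rule of section 2.8 it runs against the app. What survives is weaker: section 3 links the adoption of such technologies to better breastfeeding rates, which makes the pro-app direction the more plausible one when these women are dropped.

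A reader might also combine the wider wording in section 4 with the section 3 statement that "67.3% of the Spanish population used the Internet to obtain information on health" and conclude that most of the control arm would be lost. That does not follow. The figure describes the general population in 2018, not use of breastfeeding tools by controls. The section 4 sentences concern exchange of information about this app, and section 2.7 asks which tool was used, so LactApp use can be singled out. The difference in wording still has to be reconciled.

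Nor does the anonymized company data ("All of these data will be provided by the company in an anonymized form") make a matching rule for the app arm impossible, because women also report their own use. A detailed PP definition may stand in a fuller document. However, a control-only exclusion from the study is stated here, and it is not a missing detail.

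The best defence is that section 2.8 promises an ITT analysis and section 4 offers ITT as the answer to selection bias. But section 4 says this about dropouts, and the ITT is not named as primary. The article also does not say how women excluded from the study enter an analysis of all randomized women.

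**Conclusion.** The point holds. A control-only exclusion triggered after randomization is stated in two versions and contradicts the ITT population. The PP comparison, and any other analysis that omits these women, is not protected by randomization.

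Size and direction rest on assumptions. With 20% of controls excluded and no true effect, dropping them shifts the comparison between 5 points towards the app and 2.5 points against it as their suspension rate goes from 40% to 70%. Treating them as losses shifts it 8 to 9 points against the app at rates of 40-45%. Against a planned difference of 20 points, a choice that the article leaves open could matter to the conclusion. A true ITT analysis with observed outcomes carries none of this bias.

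**What to change.** 1. In sections 2.2 and 4, delete control-arm use of LactApp or online tools as a reason for exclusion.
2. Keep these women in follow-up and analyse them in their allocated arm with their observed outcomes. Name this ITT analysis as primary in section 2.8.
3. Use one definition of contaminating use, namely LactApp use as identified by the digital-tools item that asks which tool, and report it by arm.
4. Make the PP analysis supportive, with an adherence rule that applies to both arms, such as self-reported app use.

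This is a wording change in three sections and needs no new data item. The real cost is dilution. In the case worked above, where 20% of controls gain the full effect, power falls from about 95% to about 82%, slightly below the planned 85%. It would be lower still at the 0.005 significance level printed in section 2.8.2. Smaller contamination, or a partial effect in contaminated controls, would cost less.

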### 2.3. Randomization and Blinding

The women will be included during the third trimester of pregnancy in the different primary care midwife consulting rooms of each of the participating centers. After reading the information sheet and giving informed consent, the women will be registered on a webpage created for the purpose of the research and will be assigned to one of the groups (control or intervention) via a simple randomization process, until the estimated sample size has been reached. Randomization will be performed using Epidat v.4.2. [33], with groups of equal size.

Allocation concealment will be carried out, with blinding of the midwives in charge of recruiting the women, providing them with sealed, opaque and sequentially numbered envelopes to be delivered to each new participant wishing the participate in the study.

The research team will prepare the envelopes based on the random allocation sequence. Each envelope will contain a card with a QR code providing access to the study follow-up platform. Follow-up data collection will be conducted by another researcher blinded to the group status of participants. Only the data manager will have access to all of the integrated data (the data reported by the participating women through the surveys and the birth/postpartum data reported by the principal investigators).

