### 2.4. Sample Size Determination

Based on previous studies [15], and assuming the BF suspension rate at 6 months to be 60% in the control group versus 40% in the intervention group, with a significance level of *p* < 0.05 and a statistical power of 85%, a balanced design would require 333 women in total. Compensating for an estimated loss rate of 20%, the estimated final total sample size would be 399 women.

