### 2.10. Validity and Reliability

The entire dataset will be confirmed after collection, and any subjects found will be directly amended by the researcher. The identification of obvious errors and outliers in the data will be shown by descriptive analysis. When necessary, data will be double-checked against the original databases.

Factors such as age, education level, employment situation, and previous experience with BF may influence the results of the study. Due to randomization, decompensated key variables between groups are not expected. However, if poorly distributed characteristics are found, these variables will be included as independent variables along with the exposure variables in the multivariate analysis models.

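### Section 2.3 names both simple randomization and equal-sized groups, and neither reading controls balance within the four hospitals

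*Protocol article*

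**What the plan says.** Section 2.3 (Randomization and Blinding) says that women are assigned "via a simple randomization process, until the estimated sample size has been reached". The next sentence reads "Randomization will be performed using Epidat v.4.2. [33], with groups of equal size". On the envelopes the section says "The research team will prepare the envelopes based on the random allocation sequence", and it describes "providing them with sealed, opaque and sequentially numbered envelopes to be delivered to each new participant". It names no blocks and no strata.

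Section 2.2 places the trial in four hospitals, three in eastern Spain and one in the west. Women are recruited in several midwife consulting rooms attached to each. The expected number of participants per hospital is not given.

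Section 2.4 states that "a balanced design would require 333 women in total" and raises this to 399 for losses. Section 2.10 says "Due to randomization, decompensated key variables between groups are not expected" and adds that any characteristic found to be unevenly distributed will enter the multivariate models. It lists age, education, employment and previous breastfeeding experience as possible influences. Hospital is not on that list, nor among the baseline variables in section 2.7.

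**The concern.** Simple randomization, in its usual sense of an independent 1:1 draw for each woman, does not produce groups of equal size. If the list is built so that the totals come out equal, it is no longer simple in that sense. A reader cannot tell which procedure generated the sequence, and a trial that commits to CONSORT reporting (section 2.1) will have to say.

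The second question is the hospital. Usual care is delivered locally, so suspension of breastfeeding may plausibly differ between hospitals. Neither reading of section 2.3 keeps the arms balanced within a hospital. The only stated remedy, in section 2.10, depends on what imbalance is noticed and does not mention hospital. A hospital imbalance could therefore go unadjusted, or it could change the model after the data have been seen.

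**Working it through.** The plan gives no figure for expected balance, so there is none to reproduce. The check takes its 399 women, 1:1 ratio, four hospitals and 60% versus 40% rates as given. Hospital sizes and hospital-specific rates are assumptions.

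**1. Overall balance under simple randomization.** Let X be the number of women in one arm, X ~ Binomial(399, 0.5).
- The 2.5% and 97.5% quantiles are 180 and 219.
- P(arms differ by at most one woman) = 8.0%.
- The expected difference is 16 women.
- P(difference of 20 or more) = 32%; P(difference of 40 or more) = 4.5%.

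Under a fixed-total list the arms are equal, to within one woman because 399 is odd.

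**2. Balance within a hospital.** The table gives the chance of a split of 60:40 or worse in one hospital. It uses Binomial(n, 0.5) for simple randomization and the hypergeometric distribution (200 of 400 to each arm) for a fixed-total list.

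| Women in the hospital (assumed) | Simple | Fixed total |
|---|---|---|
| 50 | 20% | 17% |
| 100 | 5.7% | 2.8% |
| 200 | 0.6% | below 0.1% |

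For four hospitals of 100, the chance that at least one is 60:40 or worse is:
- simple: 1 − (1 − 0.0569)^4 = 0.21;
- fixed total: 0.10 (0.099 by exact calculation, since the four counts must add to 200).

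**3. What this does to the result.** With equal hospital sizes and N = 400, hospital mix alone moves the risk difference with SD ≈ 2σ/√N, where σ² is the variance of the hospital rates.
- Rates 50, 57, 63, 70%: σ² = (0.10² + 0.03² + 0.03² + 0.10²)/4 = 0.00545, so SD = 2 × 0.0738/20 = 0.0074 and the 95% limit is 1.96 × 0.0074 ≈ 1.5 percentage points.
- Rates 45, 55, 65, 75%: σ² = (0.15² + 0.05² + 0.05² + 0.15²)/4 = 0.0125, so SD = 2 × 0.1118/20 = 0.0112 and the 95% limit is about 2.2 points.

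Simulation gives the same limits for simple and fixed-total allocation. For scale, the planned difference is 60 − 40 = 20 points, and its sampling standard error with 399 women is √(2 × 0.24/199.5) = 4.9 points.

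**4. Power cost of unequal arms** (two-sided 5%, pooled formula, 60% versus 40%).
- 333 evaluable women: 95.8% with equal arms, 95.5% at 147:186.
- 222 women, the size at which this formula gives about 85%: 85.1% at 111:111, 84.5% at 96:126.

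The loss is below one point in both cases. That 333 exceeds 222 is a separate matter and does not affect this point.

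**The case against.** The strongest reply is that unstratified randomization is valid. Chance imbalance between hospitals does not bias the comparison in expectation, and the ordinary standard error already covers it. That stands, and it limits the point to clarity and a cheap gain in robustness.

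Three stronger readings are tempting, and the article does not support them.
- **That the scheme cannot produce equal groups.** This is true only if simple means independent draws. The text also allows an unblocked list with fixed equal totals, which gives equal arms to within one woman.
- **That one list serves all hospitals.** The article uses the singular for the sequence but does not say how many lists there are or how envelopes are shared out. A condensed article may leave that to the full protocol.
- **That allocation will be unbalanced by hospital.** Balance is uncontrolled, which is different. A reader might also quote a much higher risk from smaller hospitals. Four hospitals of 60, for instance, give 49%, but that is 4 × 60 = 240 women, not 399.

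It is also fair to say that section 2.10 foresees adjustment, that section 2.8.1 already plans a logistic model, and that a covariate list is commonly left to an analysis plan. What remains is that the rule in section 2.10 is triggered by the observed data and does not name hospital.

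**Conclusion.** The point holds as a contradiction to be reconciled and a low-cost improvement to the design; it is not a threat to validity. The two sentences in section 2.3 describe different procedures, and neither controls balance within the hospitals. The chance of at least one hospital at 60:40 or worse is about 21% (simple) or 10% (fixed total), assuming 100 women in each. The effect on the risk difference is at most about 1.5 to 2.2 points in 95% of trials, assuming hospital rates that range over 50 to 70% or 45 to 75%. Real hospital sizes and rates are not in the article, and these figures would change with them.

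**What to change.** State one procedure in section 2.3. The preferred wording is a separate list for each hospital, in randomly permuted blocks of varying size (for example 4 and 6) that is not disclosed to the recruiting midwives, with envelopes numbered separately per hospital. Used in order, such blocks hold the difference within a hospital to at most half the largest block, 6/2 = 3 women.

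In section 2.8.1, pre-specify hospital as a fixed factor in the primary logistic model, whether or not imbalance is seen. In section 2.10, remove the dependence of hospital adjustment on observed imbalance.

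If recruitment has started, state the procedure actually used and keep hospital in the model.

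The cost is a regenerated list and renumbered envelopes. Blocking adds slight predictability, which varying and undisclosed block sizes limit. Because each hospital recruits through several consulting rooms, one numbered series may not be opened in order. The envelope plan must deal with this, for example by lists per room or central allocation, so the change involves somewhat more than renumbering.
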